### Statistical treatment

For analysis of the results, a database will be created using the information collected from participants’ notebooks (questionnaires, interviews, physical tests and biological tests). Intention-to-treat analysis of all participants will be developed. After the intervention phase, descriptive statistics are performed with measures of central tendency and dispersion of the study variables. This is followed by inferential analysis by difference values between the outcome variables in both groups. In addition, multiple regression analysis of potential predictors is carried out to determine clinical prediction rules for severe fatigue and other effects of cancer treatment. The size of intergroup effect will be calculated (Cohen’s *d*). An effect size <0.2 reflects a negligible difference, between ≥0.2 and ≤0.5 a small difference, between ≥0.5 and ≤0.8 a moderate difference, and ≥0.8 a large difference. A value of *p* <0.05 will be considered statistically significant. SPSS V 21.0 will be used in Mac version for data analysis.

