## Methods/Design

### Design and participants

The present study is a randomized controlled clinical trial conforming to Consolidated Standards of Reporting Trials (CONSORT) guidelines, comparing an individualized program of strength and muscular endurance with aerobic training versus a control group. All variables will be measured at the beginning and the end of the 8-week intervention by the same evaluator, who will be unaware of the allocation of participants to each group. Furthermore, there will be monitoring for 6 months (24 weeks) after training for all outcome variables. Evaluations will be completed in the Area Health Patronage of Sports, Torremolinos, Spain.

GCC patients between 18 and 45 years who are due to undergo chemotherapy at the University Hospital of Málaga will be included in the study. The sample selection will be among those with performance status (PS) ≤1. Patients will be included and evaluated before the first cycle of chemotherapy and assigned to the experimental or control group randomly by using hidden envelopes. Potential participants will be contacted by the study coordinator and all doubts will be resolved before giving their written consent from each participant. The expected flowchart is shown in Fig. 1. The study had ethics approval from the Comité de Ética de la Investigación Provincial de Málaga (Consejería de Salud Servicio Andaluz de Salud, Spain). The principles of the Declaration of Helsinki are respected.

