### Measurements

During the study, course participants will complete questionnaires and interviews, and tests of physical condition and sampling of tissues and cells will also be carried out. The primary outcome will be the change in CRF as measured by the QuickPIPER questionnaire and also general health and quality of life will be evaluated by validated scales, as well as an objective assessment of physical condition by a standardized and validated dynamometer test.

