### Sample size

Version 3.1 G-Power was used to estimate the sample size and a minimum of 20 subjects per group (10 % loss) will be required “a priori” to have sufficient statistical power (80 %), alpha error (0.05) and a clinical effect Cohen’s *d* = 0.87 in the QuickPIPER scale of CRF [24].

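### The primary comparison of QuickPIPER change names no adjustment for the baseline score, which gives up precision in a trial of about 18 evaluable patients per arm

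*Protocol article*

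**What the plan says.** All of this is in the protocol article, under Methods/Design.

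- **Measurements** fixes the form of the outcome: "The primary outcome will be the change in CRF as measured by the QuickPIPER questionnaire".
- **Statistical treatment** gives the comparison in one sentence: "This is followed by inferential analysis by difference values between the outcome variables in both groups". It names no test and no covariate. The only regression in that section serves another purpose: "multiple regression analysis of potential predictors is carried out to determine clinical prediction rules for severe fatigue".
- **Design and participants** shows that the baseline score will exist for everyone: "Patients will be included and evaluated before the first cycle of chemotherapy" and "All variables will be measured at the beginning and the end of the 8-week intervention by the same evaluator". All outcomes are followed for a further 24 weeks.
- **Sample size** uses a plain two-group Cohen's d of 0.87, with no correlation or covariate: "a minimum of 20 subjects per group (10 % loss) will be required". It does not say which SD the d refers to, or whether the test is one- or two-sided.

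**The concern.** A raw change score subtracts the whole baseline value, whatever its relation to the later score. When the correlation rho between the two is below 0.5, and the SDs are equal, the change is more variable than the week-8 score alone. Adjusting for baseline subtracts only the predictive part.

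A modest rho is plausible here. Baseline precedes chemotherapy. Training lasts 8 weeks and, by the aims stated under Background, starts on day 1 of a course of three 3-week cycles (9 weeks). The post-test therefore falls within treatment.

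Two things are at stake. One is power, in a trial planned at 20 per arm. The other is the effect of chance baseline imbalance on the single estimate the trial will produce: a change score over-corrects for it and a week-8 score ignores it.

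**Working it through.** **Inputs.** From Sample size: d = 0.87, alpha 0.05, power 80%, 20 per group, 10% loss. Evaluable per arm: 20 × 0.9 = 18. Assumed, because the documents do not say: rho, equal SDs at baseline and week 8, and a two-sided test.

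**The plan's own figure.** By the noncentral t, a one-sided 0.05 test needs 18 per group, and 18/0.9 = 20, as stated. A two-sided test needs 22, and 22/0.9 = 24.4, so 25. Without adjustment, 18 per arm gives 82% power one-sided and 72% two-sided.

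**Variance of the treatment contrast**, in units of the score variance:
- change: 2(1 − rho)
- week-8 score alone: 1
- ANCOVA: 1 − rho²
- ratio ANCOVA/change: (1 − rho²)/[2(1 − rho)] = (1 + rho)/2

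This gives 0.65, 0.75, 0.85 and 0.95 at rho 0.3, 0.5, 0.7 and 0.9. With unequal SDs the change variance still exceeds the ANCOVA variance, by (SD0 − rho·SD1)², where SD0 and SD1 are the baseline and week-8 SDs. In large samples ANCOVA is therefore never the less efficient.

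**Power at 18 per arm**, two-sided 0.05. The noncentrality is the standardised effect × √(18/2) = 3 × effect, with 34 df for change and 33 for ANCOVA.

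*Reading A: d = 0.87 on the week-8 SD.* The effect is 0.87/√[2(1 − rho)] for change and 0.87/√(1 − rho²) for ANCOVA.

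| rho | effect, change | effect, ANCOVA | power, change | power, ANCOVA |
|---|---|---|---|---|
| 0.3 | 0.735 | 0.912 | 57% | 76% |
| 0.5 | 0.870 | 1.005 | 72% | 83% |
| 0.7 | 1.123 | 1.218 | 91% | 94% |

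At rho 0.8 the gain is under one point (98.0 vs 98.8%).

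*Reading B: d = 0.87 on the change-score SD.* The effect is 0.87 for change and 0.87/√[(1 + rho)/2] for ANCOVA.

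| rho | effect, ANCOVA | power, change | power, ANCOVA | n per arm for 80%: change / ANCOVA |
|---|---|---|---|---|
| 0.3 | 1.079 | 72% | 88% | 22 / 15 |
| 0.5 | 1.005 | 72% | 83% | 22 / 17 |
| 0.7 | 0.944 | 72% | 78% | 22 / 19 |
| 0.9 | 0.893 | 72% | 74% | 22 / 21 |

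*If the sentence means unadjusted week-8 scores*, power is 72% at every rho, against the ANCOVA figures of reading A.

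**Chance imbalance.** The baseline difference between two arms of 18 has a standard error of √(2/18) = 0.33 SD. Given an imbalance of that size, the change-score estimate shifts by (1 − rho) × 0.33 SD and the week-8 estimate by rho × 0.33 SD. At rho 0.5 each is 0.17 SD, against a planned effect of 0.87. ANCOVA removes this shift.

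**The case against.** **Silence is not a choice.** The article does not say that the comparison is unadjusted. Its wording is loose and could mean within-patient change or simply a between-group difference. Regressing change on arm and baseline gives the same treatment estimate, standard error and p-value as ANCOVA on week 8, so a change outcome does not exclude adjustment. A separate analysis plan could supply the covariate. This stands as a limit on certainty. Still, the article names its outcome and its comparison and gives regression a different job, so the point concerns a stated method, and it holds under either reading of the sentence.

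**Efficiency, not validity.** This stands. Under randomisation the change-score comparison is unbiased with correct type I error. Imbalance matters only conditionally, for the allocation that happens to occur.

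**The power figures lean on assumptions.** This also stands. The 57% figure exists only if d is on the week-8 SD. The ANCOVA powers deduct one degree of freedom but ignore the small variance inflation from chance covariate imbalance. Simulation under reading A gives 74, 82 and 94% where the formula gives 76, 83 and 94%. A loss of one or two points would absorb most of the gain at rho 0.9 in reading B.

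**Two stronger inferences are not supported.** A reader might infer that the trial is already below its stated power. That needs a two-sided test, which the article does not state; the one-sided calculation reproduces 20 per group exactly, and 20 is a stated minimum. A reader might also infer that change scores defeat the promise "Intention-to-treat analysis of all participants will be developed", because a lost patient has no difference value. Simple ANCOVA loses the same patients when the week-8 score is missing. That is a missing-data question and not a fault of change scores.

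**Conclusion.** The point holds as a loss of efficiency. The plan compares change, or possibly raw week-8 scores, and names no adjustment for a baseline it collects in everyone. Relative to change, adjustment cuts the variance by (1 − rho)/2: 35, 25, 15 and 5% at rho 0.3, 0.5, 0.7 and 0.9.

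In power at 18 per arm, the gain is about 19, 11 and 4 points at rho 0.3, 0.5 and 0.7 if d is on the week-8 SD. It is about 16, 11, 7 and 2 points at rho 0.3, 0.5, 0.7 and 0.9 if d is on the change-score SD. These sizes rest on equal SDs, a two-sided test and a rho that the documents do not give. The gain matters at low to moderate rho and is minor at high rho. The change should be made, but the trial is not invalid without it.

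**What to change.** In Statistical treatment, replace the sentence on the group comparison with wording such as:

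*The primary analysis compares week-8 QuickPIPER (equivalently, its change from baseline) between arms by ANCOVA with baseline QuickPIPER as covariate, and reports the adjusted mean difference with 95% CI and p-value. Continuous secondary outcomes are analysed in the same way, each with its own baseline.*

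If a repeated-measures model is preferred, so that patients with a missing visit stay in the analysis, specify one model only: week 8 and the 24-week follow-up as responses, baseline as covariate, and the week-8 contrast as primary. Baseline should not also appear among the responses.

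The ANCOVA costs one degree of freedom and a change of wording, needs no extra data, and runs in the SPSS version named. Trial status says recruitment had not opened at submission, so at that stage the change could be made before any outcome was seen.

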Metabolomics is an emerging discipline, defined as a multidisciplinary science that requires cooperation between chemists, biologists and computer scientists. Metabolome is the term used to refer to the complete inventory of small molecules, non-protein compounds, such metabolic intermediates, ATP, fatty acids, glucose, cholesterol, hormones, and other signaling molecules, and secondary metabolites found in a biological sample [13, 14]. As such, the metabolome changes continuously, depending on the activation and interaction of the various metabolic pathways inside the cell. It also reflects the phenotype that can be used to interfere gene function. Although genomics and proteomics can provide important information on expected function, metabolomics provides an immediate snapshot of all biological functions that reflect current events at a specific time [15].

The primary objective of the study is to investigate the short- and long-term (6 months) effects of an individualized program of muscular strength and endurance with aerobic training to improve CRF. A secondary goal is to examine the tolerance of muscular endurance training started on day 1 of the course of cancer treatment on muscle deterioration. Furthermore, the effect of the program on metabolomic level and on various fitness and quality-of-life parameters will be analyzed to try and establish rules of clinical prediction by multivariate regressions. The hypothesis of our study is that a program of muscular strength and endurance with aerobic training to improve CRF can be designed.

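### Forty patients, sized only for a two-group difference in fatigue, are too few to determine clinical prediction rules; the regression should be declared exploratory

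*Protocol article*

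**What the plan says.** The protocol article mentions the prediction work in three places.

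- **Background, objectives:** metabolomic, fitness and quality-of-life data are to be analysed "to try and establish rules of clinical prediction by multivariate regressions".
- **Statistical treatment:** the wording is firmer: "multiple regression analysis of potential predictors is carried out to determine clinical prediction rules for severe fatigue and other effects of cancer treatment". The database behind it draws on "questionnaires, interviews, physical tests and biological tests". No list or number of predictors is given, and no threshold for severe fatigue.
- **Discussion:** results in general are expected to reach practice guidelines promptly, while the regression in particular is described as something that might prompt further studies.

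The sample size section says that "a minimum of 20 subjects per group (10 % loss) will be required", for 80 % power at alpha 0.05 and a Cohen's d of "0.87 in the QuickPIPER scale of CRF". That is a two-group comparison. Nothing in the section concerns a prediction model.

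**The concern.** A prediction rule needs enough patients, and for a yes/no outcome enough events, for its coefficients to carry over to new patients. With too few, the model looks better in the data that built it than it will anywhere else. Here the aim is to determine clinical rules, while the trial was sized for a different question with a large assumed effect.

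The pool of measured variables is also large relative to the sample. If many of them were screened, a rule would probably appear even where none exists. A reader of the results could then take an optimistic model for a usable one.

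**Working it through.** **1. The plan's own figure.** A two-sample t-test with d = 0.87, alpha 0.05 and 80 % power needs 18 per group one-sided, and 18/0.9 = 20, which matches the article. Two-sided it needs 22 per group, or 22/0.9 = 24.4, so 25. The article does not state sidedness. Either way, the calculation concerns only the group difference. Planned total: 40; after 10 % loss: 0.9 × 40 = 36.

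**2. Severe fatigue as yes/no, three predictors.** The minimum n for expected shrinkage S = 0.9 with k predictors is

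n = k / [(S − 1) · ln(1 − R²/S)],

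where R² is an assumed fraction of the maximum Cox-Snell value, R²max = 1 − [φ^φ (1 − φ)^(1 − φ)]², and φ is the prevalence. The article gives no prevalence for men on chemotherapy. Its 30 % (Background) refers to long-term survivors, so I used a range of 20 to 50 %.

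| Assumed φ | R²max | Events in 36–40 patients | n, R² at 50 % of max | n, R² at 15 % of max |
|---|---|---|---|---|
| 0.20 | 0.632 | 7–8 | 70 | 270 |
| 0.30 | 0.705 | 11–12 | 61 | 240 |
| 0.50 | 0.750 | 18–20 | 56 | 225 |

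Example: φ = 0.50 and R² = 0.375 give 3 / [0.1 × 0.539] = 55.7, so 56.

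The requirement is proportional to k. Five predictors at φ = 0.30 need 101 to 400. Two predictors need 38 to 180 over the whole range, and one needs 19 to 90.

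**3. Size of the variable pool.** The section on secondary outcomes lists 4 medical and demographic items, 2 for SF-12, 2 for EuroQoL, 7 for POMS (the overall index and the six subscales it names), 5 strength measures, 6 inflammatory markers and 6 lipid, glucose and insulin values: 4 + 2 + 2 + 7 + 5 + 6 + 6 = 32. Metabolites come on top.

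**4. Illustration: what screening such a pool would do.** The article names no selection method; forward selection at p < 0.05 on 32 independent variables is my assumption.

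- *Pure noise.* The chance that at least one variable enters is 1 − 0.95³² = 0.81; simulation gives about 80 %. Mean apparent R², counting empty models as zero, is about 0.26 at n = 36 and 0.23 at n = 40. Median R² in new data is −0.33 and −0.25.
- *Three real predictors, true R² 0.3.* Median apparent R² is 0.47 to 0.48; in new data it is about −0.1, worse than predicting the mean.
- *Three real predictors, true R² 0.5.* On average 2.3 to 2.6 real and 1.8 to 1.9 noise variables are selected; new-data R² is 0.19 to 0.27.

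**5. Does the alternative fit this trial?** For a continuous outcome the shrinkage criterion is S = 1 + (k − 2) / [n · ln(1 − R²app)], with R²app = [R²(n − k − 1) + k] / (n − 1). With k = 3 and true R² = 0.2 it is met at n = 31: R²app = (0.2 × 27 + 3)/30 = 0.28, and S = 1 − 1/(31 × 0.3285) = 0.90. Larger R² needs fewer patients. In simulation, three fixed predictors, all real, give a positive mean new-data R² at n = 36 to 40: about 0.1 for true R² 0.2 and 0.44 for true R² 0.5.

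**The case against.** A reader might infer that at least 32 candidate predictors will be entered and that the resulting rules will be mostly noise. The documents do not support that. The 32 is a count of measured variables, most of them listed as secondary outcomes, and nothing says all are candidates. The objectives tie the rules only to metabolomic, fitness and quality-of-life data. Forward selection, unpenalised regression and untargeted metabolomics are not stated either. The noise simulation also assumes independent variables, which is unlikely for cholesterol fractions or for a mood index and its own subscales. Under a strong signal real predictors outnumber noise ones. With five prespecified predictors (three real, true R² 0.3, n = 40), only about 0.1 noise variables are selected on average.

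A reader might also infer that the rule is meant to go straight into practice. The guideline sentence in the Discussion is about the study's results generally; the objectives speak only of trying, and the Discussion treats the regression as a source of new studies.

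Finally, predictor lists, penalisation and validation may be set out in a fuller document, so their absence from the article is no fault.

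All of this stands, and it limits the point. It does not remove it: the firm wording under Statistical treatment and the sample size are both in the article, and no list of three or more predictors elsewhere changes the number of patients.

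**Conclusion.** The point holds as a mismatch between a stated secondary aim and the size of the trial. For a yes/no rule with three predictors, 36 to 40 patients fall short of the 56 to 270 needed, by a factor of 56/40 = 1.4 at best and 270/36 = 7.5 at worst. This rests on assumed ranges for prevalence and explained variation, on a shrinkage target of 0.9, and on severe fatigue being dichotomised, which the article implies but does not define. A rule with one or two predictors would meet the criterion only towards the favourable end of those ranges. The screening results illustrate a risk; they do not describe the plan. The primary comparison is untouched.

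**What to change.** - In the Background objectives and under Statistical treatment, replace the aim of determining or establishing clinical prediction rules with an exploratory, hypothesis-generating prediction analysis. This agrees with what the Discussion already says about the regression.
- Use the continuous QuickPIPER score as the outcome, with at most two or three predictors fixed in advance (for example baseline QuickPIPER and group). If more variables or metabolites are to be considered, use a penalised model.
- Report bootstrap optimism-corrected performance, repeating the whole selection process in each resample.
- State that no clinical rule will be claimed without external validation.

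The cost is a change of wording and some bootstrap code, with no extra patients or measurements. The article says recruitment had not opened at submission. The price is that one secondary claim becomes hypothesis-generating.

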## Discussion

The study results will be quickly applied in clinical practice guidelines thanks to the internal and external validity of the study, whether the hypothesis is accepted or not. Such a scheme, if beneficial, could be implemented within public health, after certain requirements are resolved with regard to resistance-training facilities, with instructors who are properly educated in order to train cancer patients undergoing chemotherapy. Patients with testicular GCC are offered an individualized program of muscular strength and endurance with aerobic training on CRF. In addition, regression analysis may open up new niche clinical studies on this question.

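### The Discussion promises guideline use whatever the result, but the trial is sized only for a large effect, and the stated hypothesis is not the one tested

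*Protocol article*

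**What the plan says.** **Use of the results.** The Discussion says its findings are to be "applied in clinical practice guidelines thanks to the internal and external validity of the study, whether the hypothesis is accepted or not". The sentence after it makes roll-out in public health conditional on benefit. The guideline sentence carries no such condition.

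**Hypothesis and objective.** The Background states: "The hypothesis of our study is that a program of muscular strength and endurance with aerobic training to improve CRF can be designed". The primary objective in the same section is to "investigate the short- and long-term (6 months) effects of an individualized program of muscular strength and endurance with aerobic training to improve CRF".

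**What is compared.** Under Measurements: "The primary outcome will be the change in CRF as measured by the QuickPIPER questionnaire". Statistical treatment plans "inferential analysis by difference values between the outcome variables in both groups", reports Cohen's d between groups, and takes p < 0.05 as significant.

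**Size.** Under Sample size, "a minimum of 20 subjects per group (10 % loss) will be required", for 80% power, alpha 0.05 and d = 0.87 on QuickPIPER. Statistical treatment grades d below 0.2 as negligible, 0.2 to 0.5 as small, 0.5 to 0.8 as moderate and 0.8 or more as large. Neither section says whether the test is one- or two-sided. The article gives no margin or rule for reading a non-significant result.

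**The concern.** The Discussion commits in advance to guideline use even if the hypothesis is not accepted. That needs a null result to be informative, yet the trial is sized only for an effect in the article's top band. If a true moderate effect is more likely to be missed than found, and the interval around a null estimate is wide, non-significance says little about whether the program helps.

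The hypothesis wording adds to this. The Discussion hangs its promise on a hypothesis being accepted or not, but the one written in the Background is satisfied once a program exists. No QuickPIPER result could refute it. At stake is what the trial may claim, chiefly if it is not significant; the primary comparison itself is not invalidated.

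**Working it through.** **Inputs.** From Sample size: 20 per group, 10% loss, alpha 0.05, power 80%, d = 0.87. From Statistical treatment: the effect-size bands. Assumed: equal groups and an unadjusted two-sample t-test. If 20 is the enrolled number, 20 × 0.90 = 18 are evaluable per group; if 20 is already net of loss, 20 are evaluable. Both are carried through.

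**1. The plan's own figure.** Power comes from the noncentral t distribution with 2n − 2 degrees of freedom and noncentrality d√(n/2).
- One-sided 0.05: 18 evaluable per group, and 18/0.90 = 20. This matches exactly.
- Two-sided 0.05: 22 evaluable per group, and 22/0.90 = 24.4, so 25.

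The stated size matches a one-sided test, but the article does not say so. Results are given both ways.

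**2. Power at the planned size.** For d = 0.5 the noncentrality is 0.5 × √9 = 1.50 (n = 18) or 0.5 × √10 = 1.58 (n = 20).

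| True d | Band | n = 18, two-sided | n = 20, two-sided | n = 18, one-sided | n = 20, one-sided |
|---|---|---|---|---|---|
| 0.3 | small | 0.141 | 0.152 | 0.223 | 0.238 |
| 0.5 | moderate | 0.308 | 0.338 | 0.431 | 0.463 |
| 0.8 | large | 0.645 | 0.693 | 0.760 | 0.799 |
| 0.87 | large | 0.718 | 0.765 | 0.819 | 0.855 |

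A true d of 0.5 is missed in 66–69% of trials two-sided and in 54–57% one-sided. For scale, 80% two-sided power at d = 0.5 needs 64 evaluable per group.

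**3. Width of the interval.** The 95% CI half-width in SD units is t(0.975, 2n − 2) × √(2/n).
- n = 18: 2.032 × 0.333 = 0.677
- n = 20: 2.024 × 0.316 = 0.640

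An estimate of exactly zero gives about ±0.68 or ±0.64, which contains the whole small band and the lower part of the moderate band. To exclude 0.5, the estimate must fall below 0.5 − 0.677 = −0.18 or 0.5 − 0.640 = −0.14, so the control group would have to look better. To exclude 0.87, it need only fall below 0.87 − 0.677 = 0.19 or 0.87 − 0.640 = 0.23.

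**4. What a null result could rule out.** If the true effect is zero, the chance that the upper 95% limit falls below a given d is:

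| d to exclude | n = 18 | n = 20 |
|---|---|---|
| 0.2 | 0.084 | 0.090 |
| 0.5 | 0.308 | 0.338 |
| 0.87 | 0.718 | 0.765 |

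With any true benefit above zero these chances are lower.

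**5. Effect of baseline adjustment.** If d is in units of the raw score's SD, adjustment multiplies the half-width by about √(1 − ρ²), where ρ is the correlation between baseline and week-8 scores. The article gives no ρ. For a zero estimate to exclude 0.5, the factor must be below 0.5/0.640 = 0.781 (n = 20) or 0.5/0.677 = 0.739 (n = 18), so ρ must exceed about 0.62 or 0.67.

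**6. Hypothesis against test.** The Background hypothesis concerns whether a program can be devised. The Intervention section already sets one out. The outcome and analysis sections compare fatigue between randomized groups. A null, favourable or unfavourable difference would leave the written hypothesis equally true.

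**The case against.** The strongest reply is that this is one promotional sentence in a Discussion and governs no procedure. The article does not say that a non-significant p-value means no benefit. It makes public-health implementation conditional on benefit, and it commits to reporting a graded Cohen's d as well as a p-value. The question actually tested can be recovered from the objective, the outcome and the analysis text, so the awkward hypothesis sentence changes no test, endpoint or sample size.

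Much of that stands. A reader might infer that the plan would send a null result to guidelines as lack of benefit; no section says so. A reader might also infer that the trial can support no negative conclusion at all. Step 4 shows otherwise: with a true effect of zero it would exclude 0.87 in about 72–76% of trials. Single examples can mislead here too. An observed d of 0.2 has an upper limit of 0.877 with 18 per group, just including 0.87, but 0.840 with 20 per group, which excludes it.

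Nor does recruitment at one hospital with limits on age and performance status contradict the article. Those are ordinary, openly stated entry conditions.

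What the reply does not remove is that the guideline sentence expressly covers the case where the hypothesis is not accepted, with no limit on how a null may be read, in a trial that would usually leave a moderate benefit open.

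**Conclusion.** The point holds as one of interpretation and wording. At the planned size, power for d = 0.5 is 31–34% two-sided or 43–46% one-sided, and the 95% CI half-width is about 0.64–0.68 SD. A non-significant result would therefore usually fail to exclude a small or moderate benefit, so guideline use whatever the outcome is not supported. Separately, the Background hypothesis cannot be tested by the planned comparison.

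The figures assume equal groups, 18 to 20 evaluable per group and an unadjusted t-test. Using d = 0.5 as the reference is a choice taken from the article's own bands; the article does not make it a decision threshold, and none is claimed here.

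**What to change.** **Hypothesis (Background).** Restate it as a between-group difference, for example: *QuickPIPER fatigue at the end of the 8-week intervention, adjusted for the baseline score, differs between the exercise and control groups.* Keep the 6-month assessment in the objective. The baseline score is already collected. With baseline as a covariate, analysing the change or the week-8 score gives the same estimated group difference, so this is compatible with the stated change outcome.

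**Discussion.** Replace the guideline sentence with, for example: *A non-significant result will be reported as the estimated between-group difference with its 95% CI and will not be read as absence of benefit.* No fixed exclusion margin is needed.

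**Cost.** No extra patients, visits or data. Naming the baseline-adjusted analysis is a small analysis decision as well as a wording change. The main downside is a less ambitious claim about a null result. Trial status says recruitment had not opened at submission, so the change could have been made before any data existed.
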